## 4 Subject Selection and Withdrawal

### 4.1 Inclusion Criteria

1. Adult subjects over 18 years of age
2. Subjects presenting with a lung, pleural nodule or mass presumed to be resectable on pre-operative assessment
3. Good operative candidate
4. Subject is capable of giving informed consent and participating in the process of consent.

### 4.2 Exclusion Criteria

1. At-risk subject populations
  - a. Homeless subjects
  - b. Subjects with drug or alcohol dependence

- c. Children and neonates
  - d. Subjects unable to participate in the consent process.
2. Female patients should not be pregnant or lactating.. Women of child-bearing potential will be included provided that they have a negative pregnancy test or provide documentation of sterilization, menopausal or post-menopausal status, prior to infusion.
  3. Patients who have received SGM-101 in the past.
  4. Patients who have received any investigational drug four weeks of the injection.

#### **4.3 Subject Recruitment and Screening**

Subject recruitment will be performed by the surgeon with subjects under his or her direct care. All eligible candidates will be invited to participate in the research in the following manner:

- 1) During the subject's initial surgical consultation, the surgeon or a member of the study team will describe the study and its risks and benefits. P.I., surgeon on the protocol, or a member of the study team will obtain consent from subject.
- 2) The day of the subject procedure, 25-50 mg of IV Benadryl may be recommended prophylactically but not required, and the study drug will be administered in the Center for Human Phenomic Research by the PI or CHPS personnel. The decision for Benadryl will be at the discretion of the principal investigator.

#### **4.4 Early Withdrawal of Subjects**

##### When and How to Withdraw Subjects

Subjects will be withdrawn from the study if one of the following considerations has been met:

1. The subject decides that they do not wish to have their surgery
2. The subject experiences a SAE or an AE during the injection which would require an intervention of steroids or epinephrine in the OR.
3. The subject withdraws consent.
4. The PI, or a member of the study team, decides that it is not in the subjects' best interest to continue.
5. The subject is non-compliant with the protocol.
6. Lost to follow up due to death

If the subject withdraws, at any time, the reason(s) will be recorded on the relevant page of the case report form. If the subject is discontinued due to AEs or ADEs, the

subject will be monitored until resolution or stability of the event based on the judgment of the investigator.

#### Data Collection and Follow-up for Withdrawn Subjects

If the subject decides to not participate in the study before their injection, it would make no impact on our study outcomes for survival data, as there is only a single procedure point. However, if the subject wishes to withdraw consent after the study, efforts will be made to secure permission to follow-up with the subject's survival and recurrence data for up to five years after their surgery.

## 5 Study Drug

### 5.1 Description

The SGM-101 active ingredient is a covalent conjugate of the SGM-Ch511 anti-CEA chimeric monoclonal antibody with the fluorochrome BM-104 (Figure III.1-1). The BM-104 fluorochrome is conjugated to free amino groups of the antibody via an amide bond.

### 5.2 Treatment Regimen

The proposed dose of SGM-101 to be explored in this study is 5-10 mg to be administered intravenously over 30 minutes followed by a 50 mL flush of isotonic saline to account for the dead volume of the tubing. SGM-101 will be administered 3 to 5 days (+/-1 day) prior to surgery..

### 5.3 Method for Assigning Subjects to Treatment Groups

There will be only one treatment group for this trial.

### 5.4 Preparation and Administration of Study Drug

The SGM-101 active substance will present as a 5.0 mg/mL solution in 10 mM KH2PO4, 10 mM Na3 citrate, 300 mM arginine, 0.02% Tween-20, pH 6.0. The SGM-101 finished product is a sterile solution for injection of the same composition. It will be supplied as 4R type I amber glass vials capped with Flurotec® elastomeric stoppers and aluminum flip-off seals, containing a nominal volume of 2.3 mL and stored at +2 to +8°C. The SGM-101 active substance and investigational medicinal product (IMP) are manufactured and controlled in compliance with good manufacturing practice (GMP) by Polymun Immunobiologische Forschung (Klosterneuburg, Austria).

### 5.5 Subject Compliance Monitoring

Treatment includes a one-time dose of study drug with no additional compliance required after surgical exploration.

## 5.6 Prior and Concomitant Therapy

No prior or concomitant therapies will be collected or prohibited during this investigation.

## 5.7 Packaging

Carton label:

**Study: SGM- CLIN03**

**SGM-101, Vial containing 2,3 mL (2ml extractable)**

**11,5mg (10 mg extractable)**

[figure not shown]

Sterile solution for I.V. injection

See separate instructions for use

Store between +2°C and +8°C

**Batch #: SGM1010618-A**

**Unit #:** \_\_\_\_\_

**Expiry date:**

**Investigator name:** \_\_\_\_\_

Sponsor Address: [name]

[contact]

*Caution: New Drug—Limited by Federal (or United States) law to investigational use*

## 5.8 Blinding of Study Drug

As this is strictly an observational imaging study, no blinding of the drug will be necessary.

## 5.9 Receiving, Storage, Dispensing and Return

IDS will be responsible for all aspects of receiving, storage, dispensing and return of the drug. Drug will be shipped from the company manufacturing the drug directly to the IDS. Upon receipt of the drug an inventory will be performed and a drug receipt log filled out and signed. The shipment will be counted and verified that it contains all the items noted in the shipping invoice. Any discrepancies, damaged or unusable study drug in a given shipment will be documented in the study files.

# 6 Study Procedures

## 6.1 Visit 1- Initial Consult (up to 90 days before surgery)

Prior to the initiation of study-specific screening assessments the Investigator or a member of the study team must provide the subject(s) a complete explanation of the purpose and evaluations (procedures and assessments) of the study. Subsequently, the subject must sign and receive a copy of an Informed consent form to examine at their leisure. Once informed consent has been obtained, the eligibility of the subject

will be determined, and screening period assessments will be performed.

## 6.2 Visit 2- CHPS (infusion up to 5 days before surgery)

Visit two will consist of the infusion of SGM-101 and surgery. Based on the discretion of the surgeon, 25 mg of Benadryl may or may not be administered prior to infusion of study drug. Once the administration of the Benadryl, is completed, the drug will be administered by the surgeon or CHPS personnel. Note that SGM-101 should not be mixed with other medicinal products and should not be given simultaneously through the same intravenous line as another medicine. During this time, the subject will be monitored by CHPS personnel for signs of an allergic reaction. Vital signs (Heart rate, Blood Pressure, Pulse/Oxygen levels, body temperature and skin color) will first be collected and recorded at pre-infusion, next at 15-minute intervals after the infusion has begun up until the 45-minute infusion is complete (see chart below). This will include the 30 minutes for the infusion of the drug and the 15 minutes for the infusion of the flush.

|            | Pre-Infusion | Infusion Start | 15 minutes after starting infusion | 30 minutes after starting infusion; end of infusion | 45 minutes after starting infusion | 60 minutes after starting infusion |
|------------|--------------|----------------|------------------------------------|-----------------------------------------------------|------------------------------------|------------------------------------|
| Time       |              |                |                                    |                                                     |                                    |                                    |
| Temp       |              |                |                                    |                                                     |                                    |                                    |
| HR         |              |                |                                    |                                                     |                                    |                                    |
| BP         |              |                |                                    |                                                     |                                    |                                    |
| O2 Sat     |              |                |                                    |                                                     |                                    |                                    |
| Skin color |              |                |                                    |                                                     |                                    |                                    |

## 6.3 Visit 3- Surgery

During the operation, imaging will take place before resection and after resection. Before resection, the surgeon will perform the standard of care operation in order to expose the tumor. Once the lung is exposed, the surgeon will use the intraoperative imaging device to videotape and discover if the tumor is fluorescent. Also, the surgeons will determine if there are any additional lesions that are fluorescent.

Once this is accomplished, we will proceed with the standard-of-care operation and resection. Then once the tumor is removed, the camera will be re-inserted to determine if there are any additional lesions still in the chest. If there is a lesion left behind, the surgeon will determine if this can be biopsied or not. If removing the additional lesion

would significantly alter the magnitude of the operation, then the nodule or residual cancer will not be removed. It can be monitored postoperatively by CAT scans. In this study, until we are confident of the false positive rate, no additional surgery will be performed based on imaging results alone. If the surgeon using his experience feels this additional location is cancer, then it will be biopsied and/or removed.

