### **Clinical Phase I: Safety Of SGM-101 In Patients With Peritoneal Carcinomatosis From CEA Overexpressing Gastrointestinal Cancer (Study # SGM-CLIN01 / Protocol # ICM-URC-2014/35 / # EudraCT : 2014-004017-87.)**

A first-in-man open-label Phase I study was conducted in Montpellier, France (protocol N°ICM-URC-2014/35) to assess the safety of a single intravenous administration of SGM-101 in patients with peritoneal carcinomatosis from CEA-over-expressing gastrointestinal cancers.

Patients were enrolled according to a 3+3 dose escalation scheme at five dose levels: 5 mg, 7.5 mg, 10 mg, 12.5 mg and 15 mg (cohorts 1 to 5). Patients were administered SGM-101 24 hours prior to surgery, and an additional treatment group at the 15 mg dose level was included in order to assess administration 48 hours prior to surgery (cohort 5 pts).

Fifteen patients were enrolled in the study as part of the dose escalation (3 per dose level). Three additional patients were enrolled at the 15 mg dose level according to the second administration scheme (*i.e.* 48 hours prior to surgery).

Visibility and background were assessed by two different and independent surgeons using fluorescent SGM-101. The two surgeons evaluated the peritoneal carcinomatosis index (PCI) without then with fluorescence, to check for the presence of additional fluorescent lesions. However, only very few efficacy data were reported in the study. Only 8 out of 18 patients underwent resection of carcinomatosis because some patients were considered unresectable during surgery due to the extent of carcinomatosis and other patients were not resected because no peritoneal carcinomatosis was confirmed during surgery, whether without or with fluorescence. And, of the 8 patients who were resected, only 3 were evaluable for efficacy due to problems with the NIR camera used in this first study so that given this small sample no conclusion was reached in regard to efficacy.

**Clinical Phase I/II : Safety of SGM-101 in Patients with Cancer of the Rectum or Pancreas (Study # SGM-CLIN02 / Protocol # CHDR1517 / EudraCT # : 2015-003281-88)**

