### 3.2 Study Endpoints

#### Efficacy

Efficacy will be assessed through determination of the sensitivity and specificity of SGM-101 uptake and expression in identifying non-small cell lung cancer. Additional exploratory efficacy outcomes will include:

- Number of lung nodules lesions identified under usual visual/tactile conditions compared with such lesions identified using SGM-101 and fluorescence imaging
- Number of lymph nodes with metastatic cancer that are identified using visual/tactile conditions compared with such lesions identified using SGM-101 and fluorescence imaging
- Proportion of subjects in whom more lesions are identified using SGM-101 with fluorescence imaging and subsequently confirmed by pathology/immunohistochemistry analysis as cancer compared with using usual visual/tactile conditions to identify such lesions
- Number of cases that surgeon cuts through tumor and the positive margin is detected by the imaging of SGM-101.

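### Three exploratory outcomes compare visual/tactile with fluorescence detection, but the camera is used before any visual/tactile finding is recorded

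*Protocol*

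**What the plan says.** Section 3.2 of the protocol, under Efficacy, makes sensitivity and specificity the efficacy measure and adds four exploratory outcomes. Three of them compare detection methods:

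- Lung lesions: "Number of lung nodules lesions identified under usual visual/tactile conditions compared with such lesions identified using SGM-101 and fluorescence imaging".
- Lymph nodes: "Number of lymph nodes with metastatic cancer that are identified using visual/tactile conditions compared with such lesions identified using SGM-101 and fluorescence imaging".
- Subjects: "Proportion of subjects in whom more lesions are identified using SGM-101 with fluorescence imaging and subsequently confirmed by pathology/immunohistochemistry analysis as cancer", again set against usual visual/tactile detection.

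The fourth concerns positive margins and is not a comparison of this kind.

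Section 6.3 gives the order of events in the operating room:

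1. Exposure: "Before resection, the surgeon will perform the standard of care operation in order to expose the tumor".
2. Camera on the tumor: "Once the lung is exposed, the surgeon will use the intraoperative imaging device to videotape and discover if the tumor is fluorescent".
3. In the same imaging step, a search for more: "Also, the surgeons will determine if there are any additional lesions that are fluorescent".
4. Only then: "Once this is accomplished, we will proceed with the standard-of-care operation and resection".
5. After the tumor is out, the camera goes back in to look for anything remaining.

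Section 3.1 places imaging before and after resection, sends nodule documentation to an electronic report form, and has the surgeon judge fluorescence live during the operation. It also recognises lesions found by the surgeon but not by the camera, without saying when the surgeon's finding is settled. Section 1.4 describes a different order in the first-in-human study, where the surgeons "evaluated the peritoneal carcinomatosis index (PCI) without then with fluorescence, to check for the presence of additional fluorescent lesions".

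**The concern.** When two detection methods are compared in the same patient, the result can be read only if each is applied without knowledge of the other or, where one must come first, its result is recorded before the second is seen. Here the index method comes first and nothing is recorded before it. The study is open-label (section 8.5) and no separate reader is named, so the surgeon who has just seen the fluorescence also says what sight and touch would have found.

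The error can run either way. A lesion noticed only because it glowed may, once felt, be entered as palpable, which understates what fluorescence adds. A lesion that the surgeon would have found by hand may be credited to fluorescence because the camera got there first, which overstates it. These three outcomes are the protocol's only direct measure of what fluorescence adds to lesion finding in usual surgery, and a pre-camera finding that was never recorded cannot be recovered afterwards.

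**Working it through.** The protocol states no figure for the visual/tactile versus fluorescence comparison, so there is nothing to reproduce. The check is a reading of the sections against each other, followed by a small calculation to show scale.

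**Step 1. What the outcomes need and what the procedure supplies.**

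| Need (section 3.2) | Supply (sections 3.1 and 6.3) |
|---|---|
| Lung lesions found by sight and touch | The only step before the camera is described as exposing the tumor; no finding is recorded |
| Metastatic nodes found by sight and touch | No visual/tactile time point for nodes |
| Subjects with more confirmed lesions by fluorescence | No rule for the method of first detection; the form has no stated order or closing point |

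**Step 2. Which lesions are exposed to the problem.** The planned nodule is already suspected on CT and PET before surgery (section 3.1), so its discovery cannot be misattributed to the camera. The risk lies with additional lesions. Section 7.2 expects one nodule per patient and says that patients with several usually do not have surgery, so additional lesions should be few and each one counts heavily.

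**Step 3. Weight of one subject.** With 20 subjects (section 7.2), one reclassified subject moves the per-subject proportion by 1/20 = 5 percentage points. Exact (Clopper-Pearson) 95% intervals:

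- 2/20 = 10%, interval 1.2% to 31.7%
- 3/20 = 15%, interval 3.2% to 37.9%
- 4/20 = 20%, interval 5.7% to 43.7%

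**Step 4. Illustration in both directions.** All inputs here are assumptions. Let t be the true proportion of subjects with more lesions by fluorescence, and q the share of those subjects whose fluorescence-only lesions are afterwards credited to sight and touch. The expected observed proportion is t × (1 − q).

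| t (assumed) | q = 25% | q = 50% |
|---|---|---|
| 10% | 7.5% | 5% |
| 20% | 15% | 10% |
| 30% | 22.5% | 15% |

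In the other direction, if 2 of 20 subjects truly had extra lesions by fluorescence and one or two more were wrongly added, the observed proportion would be 3/20 = 15% or 4/20 = 20%. Shifts of this size lie inside the sampling intervals of step 3, but the interval does not account for them. None of these rates comes from the protocol, so the table shows scale and does not estimate the bias.

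**The case against.** The strongest reply has five parts.

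*These are exploratory counts in a pilot.* True. The objectives are sensitivity and specificity (section 2), the hypotheses ask whether lung cancers fluoresce (section 7.2), and analyses are mainly descriptive. This limits the importance of the point but does not remove it.

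*The text is silent on the order of search and does not prescribe a wrong one.* Exposure leaves room for looking and feeling, and asking for additional lesions presupposes a known set. The electronic form is not shown and may capture the method of detection. This stands in part. But section 6.3 does fix when the camera is used, and no section says that a visual/tactile finding is made or entered before then. An unrecorded impression cannot anchor a count.

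*The imaging is videotaped.* That shows what the camera saw. It does not show what the surgeon would have felt without it.

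*The first-in-human study is a weak precedent.* It used two surgeons and a peritoneal index in another disease, so it sets no rule here. It shows only that the protocol's own background describes the without-then-with order.

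*Full palpation of lung and nodes before imaging could do harm.* Nodes may be reached only later in the operation, and section 1.4 notes that overlying tissue and blood can hide fluorescence. This stands. A remedy should not call for extra handling.

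A reader might also infer that the trial's main result is compromised. The documents do not support that: section 7.1 bases the primary calculation on tumor fluorescence and pathology of the single planned nodule. Nor do they support a claim that the manual search will be cut short, since sections 3.1 and 6.3 keep the standard operation in place.

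**Conclusion.** The point holds for the three comparative exploratory outcomes in section 3.2 and goes no further. Followed as written, section 6.3 lets the comparator be supplied by a surgeon who has already seen the images, so the method that first found an additional lesion can be misattributed in either direction. Primary sensitivity and specificity are unaffected.

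The size of the bias cannot be derived from the protocol. A reader might be tempted to take the 60% in section 7.1 as a per-lesion detection rate and compute a loss of added yield from it. That figure is the expected share of enrolled subjects with fluorescent tumors, and a visual/tactile detection rate and a relabelling rate would still have to be invented. What can be said is that each misattributed subject shifts the per-subject proportion by 5 percentage points. The conclusion assumes that the report form, which is not shown, does not already enforce an order of entry.

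**What to change.** In section 6.3, add a recording step before the camera is used on each exposed field, meaning the lung first and nodal stations as they are reached. Suggested wording:

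*Before the camera is used on an exposed field, the surgeon enters in the electronic report form each lesion already identified there by the usual inspection and palpation. That entry is then closed. Lesions first seen on fluorescence are entered afterwards, with fluorescence as the method of first detection.*

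This asks for no handling beyond the usual operation. The cost is a short recording pause before imaging and a field in the form for method of first detection. It has to be in place before the patients concerned are operated on. Where the order cannot be kept, section 3.2 should say that the comparison is descriptive and that the two methods were not assessed independently.

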The sensitivity will be based on the single lung nodule that is being removed in a patient. Typically for lung cancer surgery, we are there to remove one nodule. That will be the basis of the calculations. Thus, the denominator will be 10 patients for the first Cohort, and another 10 patients for the second Cohort. (A total of 20 data points for the whole study). The calculations will be based on two pieces of data: tumor fluorescence and pathology. We will not be doing a detailed IHC study at this time.

If successful, we will consider 10 more subjects. Then, with 20 subjects, we will have 90% power to identify any unforeseen adverse event that occurs with a prevalence of at least 5%. We will use a Bayesian continuous safety monitoring design that registers a signal if the posterior probability that the chance of an adverse reaction is greater than 0.1 exceeds 80%. If we encounter a safety signal, we will suspend enrollment until the issue has been addressed.

The fraction of tumors on pathology that are identified by the imaging procedure will provide an estimate of the sensitivity of the procedure. Of the 20 enrolled subjects, we expect approximately 60%, or 12, to have fluorescent tumors. With 12 tumors, an exact 95% confidence interval for sensitivity would range from (0%, 12%) if no tumors are detected up to (88%, 100%) if all 12 are detected. We will compute estimates of the sensitivity (fraction of path-positive margins that are called correctly) and specificity (fraction of path-negative margins that are called correctly), and calculate 95% confidence intervals around them. A second aim will be to estimate the sensitivity of the procedure for identifying all lesions, including lesions that were not pre-identified. Because some subjects will contribute more than one lesion, we will estimate these parameters using random effects logistic regression models (in SAS Proc Glimmix) that allow for between-subject variability. These specimens will provide independent estimates of the positive and negative predictive values of discovering satellite nodules.

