### 1.1 Background

According to the World Health Organization, lung cancer is the most common cause of cancer-related death in men and women, and is responsible for 1.5 million deaths worldwide annually as of 2017. Surgery remains the best option for subjects presenting with operable Stage I or II cancers, however the five-year survival rate for these candidates remains at a dismal 73% for Stage I and 53% for Stage II (1). The high rates of local recurrence suggest that surgeons are unable to completely detect and remove primary tumor nodules in a satisfactory manner as well as lingering metastases in sentinel lymph nodes. By ensuring a negative margin through imaging during surgery it would be possible for us to improve the rates of recurrence free subjects and thus overall survival.

Over the last several years, our group has taken a novel approach to the surgical approach (2-5). Specifically, we have started injecting contrast agents that go selectively to tumors and allow them to fluoresce. We postulate that provides an additional tool in the operating room for surgeons to find tumors and their margins.

Thoracic malignancies are the ideal disease to investigate intra-operative imaging. Over 25-65% of lung and pleural malignancies express carcinoembryonic antigen (CEA), therefore making CEA a target for imaging agents (6-11). Interestingly, there is minimal expression of CEA in normal lung, therefore, the background to noise of CEA in cancers versus normal lung is very high. Unfortunately, unlike colorectal cancer, it is not evident that serum CEA levels correlate with lung cancer, specifically non-small cell lung cancer.

CEA is a glycoprotein product of the gene CEACAM-5 and is a member of the immunoglobulin superfamily that serves as a cell-adhesion molecule and may also have an effect on innate immunity. High serum CEA levels have been identified as a prognostic factor in both resected NSCLC and in metastatic disease (6, 7, 11-13).

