### 3 Study Design

#### 3.1 General Design

Subjects will be seen in a General Thoracic Surgery clinic. If they have a lung nodule that is suspicious for a lung non-small cell lung cancer, they will be a candidate for the operation. From our prior experience, we have an 90% positive predictive value based on CAT and PET scans that a subject with a suspected lung cancer will in fact have lung cancer. The subjects with lung and pleural nodules will be prospectively consented to participate in this trial. There will be no randomization or control group and only subjects previously scheduled to undergo surgery will be eligible to participate. We anticipate a 24-month period will be necessary to reach our accrual goal of 20 subjects.

After obtaining informed consent, subjects will receive a one-time dose of 5 to 10 mg of SGM-101, up to 5 days prior to the planned operation. As a prophylactic measure, we may recommend giving 25 mg of IV Benadryl to the subject prior to the infusion of SGM-101 to ensure possibility of allergic reaction is absolutely minimized. This will be at the discretion of the principal investigator. The goal of surgery in subjects is to remove the nodule and lymph nodes in concern. During surgery, we will take images with an intra-operative camera system. Imaging will take place prior to surgical resection to record the localization of tumors, and post-resection to document the visualization of any residual tumor. All documenting of nodules will take place in an electronic report form.

Our analysis will be the following:

| Data Analysis of a Diagnostic Test |                    | Test result                                        |                                                   | Data Analysis                                                             |
|------------------------------------|--------------------|----------------------------------------------------|---------------------------------------------------|---------------------------------------------------------------------------|
|                                    |                    | True
(accept $H_0$ )                            | False
(accept $H_A$ )                          |                                                                           |

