## 7.2 Statistical Methods

All data will be summarized, with means and standard deviations for continuous variables and proportions for categorical variables. Graphical techniques will be used for data exploration. Analyses will be primarily descriptive. The remainder of the statistical approaches is described above.

Null hypothesis = Lung cancers will not fluoresce with a CEA-targeted dye.

Alternative hypothesis = Lung cancers will fluoresce with a CEA-targeted dye.

Alpha = 0.25

Beta = 0.5

There are 20 patients, thus the denominator will be 20.

Each patient will contribute one nodule or cancer to the study.

Patients with more than one nodule typically do not get surgery because that represents metastatic disease and is considered non-surgical.

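### Section 7.1 overstates the precision of the primary sensitivity estimate: the printed 12-point exact intervals are miscalculated, shown only at 0% and 100% detection, and use fluorescent tumors as the denominator

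*Protocol*

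**What the plan says.** Protocol section 7.1 gives the planning figure: "Of the 20 enrolled subjects, we expect approximately 60%, or 12, to have fluorescent tumors". It then states the precision: "With 12 tumors, an exact 95% confidence interval for sensitivity would range from (0%, 12%) if no tumors are detected", and "up to (88%, 100%) if all 12 are detected". No other detection rate is illustrated.

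The same section defines the quantity being estimated: "The fraction of tumors on pathology that are identified by the imaging procedure will provide an estimate of the sensitivity of the procedure". The definitions above it count a cancer that does not fluoresce as a false negative, so such a cancer belongs in the denominator of sensitivity. Section 7.2 adds "There are 20 patients, thus the denominator will be 20", with one nodule per patient.

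Two other places bear on the 60%. Section 1.1 says "Over 25-65% of lung and pleural malignancies express carcinoembryonic antigen (CEA"). Section 3.1 says of patients with suspected lung cancer that "we have an 90% positive predictive value based on CAT and PET scans". The eligibility criteria in section 4 do not select on CEA. The Protocol does not link the 60% to either figure or give any other source for it.

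**The concern.** Sensitivity is the primary endpoint in the Study Summary, and these sentences are the only statement of how precisely 20 subjects will estimate it. A reader takes from them that the interval will be about 12 points wide. Three things make that too favourable: the limits do not look like exact 95% limits for 12 observations; the illustrated results, none detected and all detected, are not results the plan expects; and the 12 in the denominator are tumors already expected to fluoresce. A tumor counts as detected when it fluoresces, so among fluorescent tumors detection is close to 100% by construction, and a result of 0 of 12 has no clear meaning.

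At stake is whether those who approve the study, or later read its result, know that it can locate sensitivity only very roughly.

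**Working it through.** **Inputs.** 20 subjects, one nodule each (7.1, 7.2). 60% of enrolled with fluorescent tumors (7.1). 90% predictive value for cancer (3.1). CEA expression 25% to 65% (1.1). Exact 95% intervals (Study Summary, 7.1).

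**1. The planning count.** 0.60 × 20 = 12. This reproduces.

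**2. The printed limits.** For 0 of n the exact (Clopper-Pearson) two-sided 95% upper limit is 1 − 0.025^(1/n). With n = 12 this is 1 − 0.025^(1/12) = 26.5%. By symmetry the lower limit at 12 of 12 is 73.5%. The printed 12% and 88% are not reproduced.

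Other conventions for 0 of 12 do not rescue them:
- one-sided 95%: 1 − 0.05^(1/12) = 22.1%
- Wilson: 24.2%
- rule of three: 3/12 = 25%

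A two-sided exact limit of 12% needs about 28 to 29 tumors (12.3% at 28, 11.9% at 29).

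**3. The denominator.** By the Protocol's definition it is pathology-confirmed cancers: 0.90 × 20 = 18 expected.

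**4. The expected number of fluorescent cancers.** If only CEA-expressing cancers fluoresce and all of those are visible:
- at 25%: 18 × 0.25 = 4.5
- at 65%: 18 × 0.65 = 11.7

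Twelve requires 12/18 = 66.7% of cancers to fluoresce.

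**5. Exact 95% intervals over 18 cancers across that range.**

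| Detected | Estimate | Exact 95% interval | Width (points) | Half-width |
|---|---|---|---|---|
| 5/18 | 28% | (10%, 53%) | 44 | 22 |
| 8/18 | 44% | (22%, 69%) | 48 | 24 |
| 12/18 | 67% | (41%, 87%) | 46 | 23 |

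**6. Where the gap comes from.** The printed width is 12 points. Correct arithmetic at the same extremes and n = 12 gives 26.5. Moving to n = 18 alone narrows the extremes to 18.5 points (0/18: 0% to 18.5%), so the denominator correction by itself works in the trial's favour. Moving from the extremes to detection rates the plan could expect brings the width to 44 to 48. Keeping n = 12 at interior rates would be wider still: 6/12 gives (21%, 79%) and 9/12 gives (43%, 95%).

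**7. Sensitivity to the 90%.** If all 20 subjects have cancer, 12/20 gives (36%, 81%), a width of 45 points. The conclusion does not depend on the 90%.

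**The case against.** The strongest reply is that the study is a pilot, its analyses are mainly descriptive, and no decision rule uses the 12 or the interval width; the rule for going on after the first cohort concerns false positives only. That is right. It limits the consequence, but does not make a printed precision figure correct.

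A reader might also infer that the 60% contradicts the Protocol, because 12 of 18 is 66.7% and the quoted CEA range ends at 65%. The documents do not support that. The top of the range gives 11.7, which rounds to 12; the text says approximately 60%; and section 1.1 introduces its range with the word over. The shortfall is 0.3 of a subject. If the range is applied to all 20 subjects, whom the Study Summary calls lung cancer subjects, it gives 5 to 13, and 12 lies inside. Nor does the Protocol say that only CEA-expressing tissue fluoresces; it provides for fluorescent nodules that are not cancer.

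Finally, the assumed rate hardly moves precision: 12/18 gives nearly the same width as 5/18 or 8/18. This reply stands. The overstated precision comes from the limits and the choice of extremes, not from the 60%.

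**Conclusion.** The stated precision is wrong and too favourable. At the Protocol's own n = 12 the exact intervals at the extremes are 26.5 points wide, more than twice the 12 printed. For the estimate as the Protocol defines it, over about 18 cancers and at rates its background makes plausible, the width is 44 to 48 points, about four times the printed figure. This rests on 90% of the 20 subjects having cancer and on one nodule per subject.

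The 60% is a lesser matter: it is underived and optimistic, at the very top of 4.5 to 11.7, but not inconsistent with the other inputs. That range also assumes that only CEA-expressing cancers fluoresce and that every one of them is seen. Two further inferences go too far. The Protocol gives no central value for CEA expression, so a count near 8 is an illustration and not what the background predicts. And a count below 12 would not be a failure under any rule in the Protocol.

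**What to change.** In section 7.1:

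- Delete the intervals (0%, 12%) and (88%, 100%). Replace them with exact 95% intervals over about 18 pathology-confirmed cancers: 5/18 (10%, 53%), 8/18 (22%, 69%) and 12/18 (41%, 87%).
- State that sensitivity will be estimated to within about plus or minus 22 to 24 points.
- State that the denominator of sensitivity is cancers confirmed on pathology, and bring the sentence in section 7.2 that sets the denominator at 20 into line with this.
- Describe 12 as the upper end of an expected range of about 5 to 12 fluorescent cancers, with the two assumptions named, or cite the evidence for 60%.

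The cost is a few reworded sentences. Enrolment, procedures and analysis do not change. The only downside is a less favourable stated precision.
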